### Sample size

The sample size for a feasibility study should be adequate to estimate the uncertain critical parameters (SD for continuous outcomes; consent/recruitment rates, attrition, intraclass correlation coefficient (ICC)) needed to inform the design of the full RCT with sufficient precision. As a feasibility study we propose to recruit for a fixed time (T) and not a sample size (N). We propose to recruit for 6 months at between 4 and 7 sites (e.g.: 4 × 6 = 24 site*months of recruitment). We believe that in order for the main trial to be feasible we need to recruit enough participants to run a full SPACES intervention group in the intervention arm at each site (recruiting at least 2*6 = 12 participants) which would be a rate of 12/6 = 2 participants per site per month. There are several flat rules of thumb for sample sizes for two-armed external pilot/feasibility trials ranging from 24 in total [31], to 30 [30, 32], to 50 or 60 [33], and 100 [34] and recruiting for 24 site*months should enable us to exceed these ranges (of 48 to 140 participants).

Interviews will be conducted with 15 participants from the intervention group and 5 intervention delivery staff members (see supplementary material for the topic guide). This sample size will be continuously evaluated during data collection process’ to ensure adequate qualitative sample size information power is met [35]. A combination of purposive and convenience sampling will be utilised to ensure adequate and varied sampling across all involved NHS sites (2–4 participants and × 1 PAC per site) from the cohort of participants and delivery staff available.

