### Recruitment

#### Recruitment of NHS sites

Sites were recruited to the SPACES programme via email invitation. Emails were sent to all mental health NHS Trust teams who had provided a letter of support for the SPACES grant application, with details of the SPACES feasibility trial. In addition, mental health NHS Trust teams with a working relationship to the research team were also approached as potential sites. Seven trusts responded to the call, at which point further information was provided regarding the trial and clarification was offered to any questions trusts had about the trial. One site was lost during this process, leaving six trusts to participate in the SPACES feasibility trial.

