We will also include, as part of the feasibility analysis, estimation of the effect size for accelerometer-determined physical activity 6-months post-randomisation (the probable primary endpoint for the definitive study), defined as the mean (averaged over all available valid days) minutes of MVPA per day, with confidence interval estimates to check that the likely effect is within a clinically relevant range (as confirmation that it is worth progressing with the full trial (i.e. 95% CI includes a difference of 6 min of MVPA per day)). For this we will use a partially clustered mixed effects model with 6-month minutes of MVPA as the outcome and baseline minutes of MVPA, site and randomised group as fixed effects and SPACES intervention groups as random effects. The ICC from this model will be reported and will inform the ICC estimate for the main trial. This information along with the acceptability of the study design and protocol to patients/GPs; the safety of the intervention; adherence to the intervention, patient recruitment and attrition/retention rates will enable us to determine whether or not the definitive RCT is feasible, within a satisfactory timescale and cost envelope using UK sites alone.

We will estimate the intervention costs based on the delivery of the related activities and the study records over the intervention period. We will also test the feasibility and acceptability of the bespoke health care and service use questionnaire. Analysis of the completeness of participants’ responses and use of listed services together with additional services recorded by participants, will enable further revision to collect most relevant data in the full RCT and eliminate questions with few responses. The completeness and descriptive statistics of healthcare resources and EQ-5D-5L will be summarised by participants’ allocated study arm. No formal cost-effectiveness analysis will be undertaken as the feasibility study is not sufficiently powered.

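### The intervention-group ICC is listed among the parameters to be estimated with sufficient precision, but about one group at each of 4 to 7 sites leaves it far too imprecise for that aim

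*Protocol article*

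**What the plan says.** All references are to the protocol article.

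- **Sample size** sets the criterion: "The sample size for a feasibility study should be adequate to estimate the uncertain critical parameters". The bracketed list that follows ends with the ICC: "intraclass correlation coefficient (ICC)) needed to inform the design of the full RCT with sufficient precision".
- The same section fixes the layout: "We propose to recruit for 6 months at between 4 and 7 sites". The aim is to recruit enough to "run a full SPACES intervention group in the intervention arm at each site", that is, "recruiting at least 2*6 = 12 participants" per site. The remaining support for the sample size is a set of flat rules of thumb on total numbers.
- **Recruitment of NHS sites** reports the number obtained: "leaving six trusts to participate in the SPACES feasibility trial".
- **Intervention description** puts 6 to 12 participants in a group. **Sequence generation** gives 1:1 allocation with a separate schedule for each site.
- **Statistical methods for primary and secondary outcomes** specifies a partially clustered mixed model for 6-month MVPA. Baseline MVPA, site and arm are fixed, and intervention group is random. It continues: "The ICC from this model will be reported and will inform the ICC estimate for the main trial".

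The article states no ICC value, no precision target for it, no external source and no caution about the number of groups.

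**The concern.** Precision of an ICC depends mainly on the number of clusters, and the sample-size argument never addresses that number. It speaks only of recruitment time, one full group per site and total participants. Clustering is in the intervention arm alone, so the clusters are the intervention groups, about 4 to 7 in all.

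The fixed site effect narrows the information further. With one group per site, a group effect shows itself only as variation between sites in the intervention-minus-control difference. That leaves the number of sites minus 1 degrees of freedom. Any true site-by-arm variation falls into the same component and cannot be separated from it.

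The ICC feeds the size of the main trial. An estimate at zero would suggest that no allowance for clustering is needed. A high one could make the main trial look unaffordable. The methods section says that feasibility within an acceptable cost is one of the things this study is to settle.

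**Working it through.** **Inputs from the article.** Sites K = 4 to 7 (six obtained). About one intervention group per site (inferred). Group size m = 6 to 12, with as many controls per site under 1:1 allocation. Site and arm fixed, group random.

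**Assumptions.** True ICC ρ of 0, 0.05 or 0.10. Balanced groups, no attrition, baseline covariate omitted. Direct REML fits that included a baseline covariate, at ρ = 0.05, gave similar zero rates: 51%, 49% and 40% for 4 groups of 6, 6 groups of 6 and 7 groups of 10.

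**The plan's own figure.** 4 sites × 6 months = 24 site-months, and 24 × 2 = 48, the lower end of the stated range. The upper end of 140 equals 7 sites × 20, which is one group of 10 plus 10 controls per site. Both ends are covered below.

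**Formula.** The arm difference at a site has variance σ_u² + 2σ_e²/m. Let S² be the sample variance of the K differences (K − 1 df), and s² the pooled within-cell variance (2K(m − 1) df). Then

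- F = (m/2)·S²/s², distributed as λ·F(K − 1, 2K(m − 1)), with λ = 1 + (m/2)·ρ/(1 − ρ).
- In the balanced case the REML estimate is θ = max{0, (2/m)(F − 1)}, and the estimated ICC is θ/(1 + θ).
- Hence P(estimate = 0) = P{F(K − 1, 2K(m − 1)) < 1/λ}.

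**Example, 6 groups of 6, ρ = 0.05.** λ = 1 + 3 × 0.0526 = 1.158, and 1/λ = 0.864. With 5 and 60 df, P(zero) = 0.49. The 90th percentile of F(5, 60) is 1.946, so F = 1.158 × 1.946 = 2.253, θ = 1.253/3 = 0.418, and the ICC is 0.295. The 97.5th percentile of F(5, 60) is 2.786, which gives 0.43 in the same way.

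| Groups × size | df | P(zero), ρ = 0.05 | 97.5th percentile, ρ = 0.05 | Median 95% CI, ρ = 0.05 | P(zero), ρ = 0.10 |
|---|---|---|---|---|---|
| 4 × 6 | 3 | 53% | 0.50 | 0 to 0.80 | 47% |
| 6 × 6 | 5 | 49% | 0.43 | 0 to 0.64 | 41% |
| 7 × 10 | 6 | 42% | 0.30 | 0 to 0.48 | 30% |
| 7 × 12 | 6 | 40% | 0.28 | 0 to 0.44 | 27% |

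Simulation with 200,000 trials per setting agrees. With a true ICC of 0, the estimate is zero in 57% to 60% of trials, yet the median upper confidence limit is still 0.36 to 0.77 over the layouts examined.

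**Is the fixed site effect the cause?** Only in part. If site is left out (ρ = 0.05), the median 95% CI is still 0 to 0.50 for 6 groups of 6 and 0 to 0.34 for 7 groups of 12.

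**Consequence if the point estimate were relied on.** Take illustrative main-trial groups of 9, equal total variance in both arms, an unclustered control arm and a true ICC of 0.05.

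- Intervention-arm design effect: 1 + 8 × 0.05 = 1.4. For the comparison: (1.4 + 1)/2 = 1.2.
- Planned with ICC = 0 at 90% power: (1.960 + 1.282)/√1.2 = 2.959, and Φ(2.959 − 1.960) = 0.84. At 80% planned power the same steps give about 72%.
- Planned at the 90th percentile for 6 groups of 6 (about 0.30): 1 + 8 × 0.30 = 3.4, and (3.4 + 1)/2 = 2.2, against a true 1.2.

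**The case against.** - **To inform is not to adopt.** A reader might infer that the main trial will take over this point estimate. The article does not say so. It treats the main-trial ICC as a separate, later estimate and excludes neither outside data nor a sensitivity range. This stands, and the consequences above are therefore conditional.
- **The precision statement is an aim.** The wording says what the sample should achieve and gives no figure. That is fair, but it is the criterion the section sets for this sample, and for the ICC the layout cannot meet it.
- **The variance is identified.** A reader might conclude that the ICC cannot be estimated at all. That goes too far: controls at each site fix the site effect, so a group variance can be estimated. The fault is imprecision.
- **One group per site is an inference.** A second group at a well-recruiting site is not excluded. It would not rescue the aim: with 20 one-per-site groups and a true ICC of 0.05, the median 95% CI is still 0 to 0.32 (groups of 6) or 0 to 0.23 (groups of 12).
- **Mixing with site-by-arm variation may be harmless.** If the main trial also runs one group per site, the combined component is what inflates its variance. This stands for that layout, but the article does not fix the main-trial layout.
- **Confidence intervals are already the stated emphasis, and main-trial sizing belongs elsewhere.** The methods section does favour interval estimation. An interval would reveal the imprecision, but it does not make the stated aim attainable.
- **Little in this trial turns on the ICC.** Feasibility is judged primarily on recruitment, and no ICC threshold is set. This also stands: the point touches no participant and not the traffic-light decision.

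**Conclusion.** The concern holds as a mismatch between a stated aim and a stated design. Across the whole planned range of 4 to 7 sites and groups of 6 to 12, the ICC is estimated far too imprecisely to satisfy the precision criterion in the Sample size section. At an assumed true value of 0.05, the estimate is zero in 40% to 53% of trials. At 0.10 it is zero in 27% to 47%.

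The cost to the main trial arises only if the estimate is relied on, and it is moderate on the low side: 90% planned power becomes about 84% with groups of 9 and a true ICC of 0.05. On the high side, the allowance for clustering could be about 2.2-fold where 1.2-fold is needed.

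These figures rest on the assumed ICCs, one group per site, balance and no attrition; loss to follow-up would worsen the precision. The correction is worth making because it is cheap and bears on how the next trial is sized.

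**What to change.** 1. In the Sample size section, take the ICC out of the parameters said to be estimated with sufficient precision.
2. In the statistical methods section, say that the ICC will be reported descriptively with a 95% CI. Note that it rests on a handful of groups and that, with one group per site, it includes site-by-arm variation.
3. State that the main trial will be sized over a range of ICCs supported by external data on group interventions (0.01 to 0.10 could serve as an illustration), and not from this estimate alone.

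Follow-up is complete according to the Trial status section, so these changes now apply to the report of this study and to main-trial planning. They need no new data. The cost is a few sentences and a small sensitivity table in the main-trial sample-size calculation.

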#### Interim analyses

No interim analyses are planned for this trial.

#### Methods for additional analyses (e.g., subgroup analyses)

Qualitative data will be analysed utilising an inductive approach and thematic analysis [40] to explore both participants and intervention delivery team experiences of the SPACES intervention. Participant data will be categorised to understand different perspectives. Qualitative analysis software, NVivo, will be used to process and analyse the data. Feedback from both participants and PACs will inform refinement of the intervention, including the intervention manual and training, with the aim to improve the acceptability and feasibility of the SPACES intervention.

Critical variables to enable success in the full RCT (workstream 3) will follow a traffic light system with recruitment of 100%, i.e., an average of 2 participants per centre per month being green, 50–99% (1 – 1.9 participants per month) being amber, and below 50% being red. This will enable us to select the correct number of centres for the full RCT. We will also test our ability to achieve follow-up at our target rate in the feasibility study, and to ensure there is equal retention between arms.

#### Methods in analysis to handle protocol non-adherence and any statistical methods to handle missing data

We will analyse the data on an intention to treat basis, whereby all participants recruited in the study will be entered into the analysis, regardless of whether or not they dropped out or partially adhered to their treatment method.

The planned primary outcome measure for the future trial, minutes of MVPA at 6 months, will be analysed at in a multiple linear regression model to compare the intervention versus usual care.

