#### Implementation

The study statistician will generate an allocation sequence. At the second baseline data collection point (accelerometer return), the SPACES researcher will contact the SPACES central team to be provided with the participant’s randomisation assignment. Participants are then told their allocation.

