### Statistical methods

#### Statistical methods for primary and secondary outcomes

As the trial is a pragmatic parallel group RCT design the statistical analysis will be performed on an intention-to-treat-basis and will be reported and presented according to the CONSORT statement extension to feasibility trials [36]. As a feasibility study the analysis will be mainly descriptive and focus on confidence interval estimation and not formal hypothesis testing.

We will use the data from this feasibility study, including reported rates of consent, recruitment and follow-up, and outcome measures, accelerometer-assessed minutes of MVPA per day (averaged over all available valid days), accelerometer-assessed total physical activity and minutes per day of sedentary behaviour (averaged over all available valid days), BMI, AIM, PHQ-9, SF-12, SIMPAQ, EQ-5D-5L, ReQoL to summarise overall and by randomised group, to inform sample size estimation for the main trial.

Accelerometer parameters will include daily 16-h per day wear time to constitute as valid wear time, intensity gradient cut off points of < 30 mg, 30–100 mg, 101–400 mg and > 400 mg (inactive, light, moderate and vigorous activity respectively). Mean MVPA per day is calculated on 5-s epochs with a 1-min bout duration, inclusion criteria of > 80%. All days (≥ 4 valid days), weekends (≥ 1 valid days) and weekdays (≥ 3 valid days) will be calculated. Mean acceleration and intensity gradients will also be reported. ActiGraph GT9X link [37] and Axivity AX6^1^ [38] accelerometers will utilise 100-Hz measurement frequency rates. Accelerometer data will be processed using GGIR v2.4–0 [39] in R [http:/cran.r-project.org].

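### The protocol says every recruited participant is analysed whether or not they dropped out, but its stated MVPA models can use only people with valid 6-month accelerometry, and nothing stated keeps the rest

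*Protocol article*

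**What the plan says.** The general principle, under *Statistical methods for primary and secondary outcomes*, is that "the statistical analysis will be performed on an intention-to-treat-basis". The later section on protocol non-adherence and missing data spells this out: "all participants recruited in the study will be entered into the analysis, regardless of whether or not they dropped out". The sentence goes on to cover partial adherence to treatment.

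Two descriptions of the MVPA analysis follow from this:

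- *Statistical methods for primary and secondary outcomes* specifies the following: "partially clustered mixed effects model with 6-month minutes of MVPA as the outcome and baseline minutes of MVPA, site and randomised group as fixed effects", with the SPACES intervention groups as random effects. Its 95% confidence interval is checked for whether it includes 6 minutes of MVPA per day, as support for proceeding to the full trial, and its ICC informs the main trial.
- The missing-data section says that 6-month MVPA "will be analysed at in a multiple linear regression model to compare the intervention versus usual care". It names no covariate and no method for missing values.

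Whether a participant has an MVPA value depends on "daily 16-h per day wear time to constitute as valid wear time", with at least four valid days for the all-days summary. Table 1 schedules accelerometry at baseline, 3 months and 6 months.

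**The concern.** The missing-data section makes a claim about who is analysed that the stated models cannot deliver. With one outcome per person, a participant without a 6-month value contributes nothing to the treatment comparison. A random effect for intervention group does not change that.

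Missing 6-month values are foreseeable. The retention section defines withdrawal from follow-up and full withdrawal, both of which end outcome collection. A participant can also attend at 6 months and still fall short of four 16-hour days.

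The estimates that inform progression would therefore rest on people who stayed and wore the device. Only one arm is offered an 18-week programme, so loss could differ between arms. The article itself treats equal retention as something to check. A smaller analysed set also widens the interval, and for a given point estimate a wider interval includes 6 minutes per day more easily. So the loss of data does not make that check stricter.

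**Working it through.** **Inputs from the article**

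- Recruitment: 2 participants per site per month for 6 months, at 4 to 7 sites (*Sample size*).
- Sites taking part: six trusts (*Recruitment of NHS sites*).
- Attrition or invalid-wear rate: none given. A target follow-up rate is mentioned without a figure.

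**The plan's own figure.** 4 sites × 6 months × 2 = 48, which reproduces the lower end of the expected range of 48 to 140.

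**Illustrative size.** Six sites × 12 participants = 72.

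**Who can enter each model**

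| Data held by the participant | Regression in the missing-data section | Mixed model with baseline MVPA |
|---|---|---|
| Valid baseline and 6-month MVPA | yes | yes |
| Valid 6-month, invalid baseline | yes, if baseline is not a covariate | no |
| Valid 3-month, no valid 6-month | no | no |
| No valid follow-up | no | no |

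The all-participants statement would need a yes in every row. As a check, 72 participants were simulated, with outcomes set missing at about 20% and baselines at about 5%. Linear regression on baseline, site and arm used 59 of the 72, exactly those with both values.

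**Number analysed.** n = N × (1 − m6), where m6 is the assumed proportion without valid 6-month MVPA:

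| N | m6 = 10% | m6 = 40% |
|---|---|---|
| 48 | 48 × 0.90 = 43.2 | 48 × 0.60 = 28.8 |
| 72 | 72 × 0.90 = 64.8 | 72 × 0.60 = 43.2 |
| 140 | 140 × 0.90 = 126.0 | 140 × 0.60 = 84.0 |

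For N = 72 that leaves about 43–65 people. If a further 10% of those lacked a valid baseline (an upper assumption), the mixed model would have 64.8 × 0.90 = 58.3 down to 43.2 × 0.90 = 38.9.

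**What joint modelling could restore.** Only people in the third row of the first table (valid 3-month but no valid 6-month wear) are regained, and only to the extent that 3-month MVPA predicts 6-month MVPA. The article gives neither their number nor that correlation, so the gain cannot be calculated.

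**The case against.** The strongest defence is that the sentence is an ordinary intention-to-treat statement about leaving treatment. Withdrawal from the intervention alone keeps follow-up data, so on that reading there is no conflict. The reading is strained. The same sentence lists partial adherence separately, the retention section speaks of withdrawal and dropout from the study, and the section heading covers missing data.

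It is also fair that the article nowhere says complete case. A reader might infer that it commits to such an analysis, but that goes too far. The model could be fitted after imputation, and an unseen SAP may say so. The conflict is between the population that the article states and the models that it states.

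Three further inferences are tempting and not supported:

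- *That many baselines will be missing.* Randomisation follows completion of baseline measurement, and people unwilling to wear the device are excluded. No check of valid wear before randomisation is stated, so some loss is possible, but it is probably small.
- *That the whole loss of precision is caused by the model.* Comparing with all 72 fully observed sets a standard that no analysis can reach, because unobserved 6-month outcomes carry information that cannot be fully recovered.
- *That the SD sizing the main trial comes from this model.* The article takes its sample-size inputs from summaries overall and by group. The model supplies the effect interval and the ICC.

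Finally, the analysis is mainly descriptive, and retention by arm will be examined. This limits the consequence but does not correct the stated analysis population.

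**Conclusion.** The point holds as an inconsistency in the stated analysis population, together with unused 3-month data. As written, the effect interval and ICC would come from participants with valid 6-month accelerometry (and valid baseline accelerometry for the mixed model), while the text describes them as everyone recruited.

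The size is uncertain because the article gives no attrition rate. The illustration of 43–65 of 72 rests on an assumed 10–40% missing at 6 months and no baseline loss. Whether the remaining set is biased, or differs between arms, cannot be judged from the article. The change is worth making because the model's output feeds the progression decision, but the impact is moderate in a feasibility trial that does no formal hypothesis testing.

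**What to change.** 1. Reword the missing-data section to say that participants are analysed as randomised, including all with at least one valid follow-up MVPA. Report by arm how many are excluded.
2. Fit 3- and 6-month MVPA jointly with a treatment-by-time term, keep the partial clustering by intervention group, and report the 6-month contrast. Participants with valid 3-month but not 6-month wear then contribute under a missing-at-random assumption.
3. Mean-impute any missing baseline MVPA, so that no one is dropped for the covariate.
4. State a fallback. If the joint model does not converge, use the mixed model already described, presented as an analysis of participants with observed 6-month data.

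No new data collection is needed. The cost is some wording, a little more analysis work, and a somewhat more complex model with within-person covariance in a small sample with few intervention groups. Anyone with no valid follow-up MVPA is still left out, which is why the wording and the counts by arm matter whichever model is fitted.

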#### Intervention description

The SPACES intervention aims to support people with SMI to initiate and maintain physical activity. The intervention comprises two core components, an 18-week group-based physical activity component and a one-to-one consultation component, both of which are facilitated by a physical activity coordinator (PAC: NHS staff with suitable experience to deliver the intervention). Suitable PAC experience will include previous history of delivering physical activity interventions to those with SMI and relevant physical activity delivery training and qualifications. The intervention will last up to 20 weeks (one-to-one consultations are offered prior to the physical activity component), with participants being offered up to 18 group physical activity sessions, up to 10 one-to-one sessions consisting of 3–6 long form consultations (30–60 min) and 2–4 check-ins (15–30 min). The intervention group will include between 6–12 participants and be supported by two PACs (four to six are trained at each NHS site for programme continuity e.g., covering annual leave). All PACs will receive training and a PAC manual on how to deliver the intervention to aid consistency. PACs will also receive ongoing bi-weekly support from the SPACES central team during the intervention delivery.

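### The 6-month MVPA comparison is given two unranked models, one with a random effect for intervention groups and one an ordinary regression without it

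*Protocol article*

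**What the plan says.** In the protocol article, *Statistical methods for primary and secondary outcomes* plans to estimate the effect on accelerometer MVPA at 6 months and to check whether the "95% CI includes a difference of 6 min of MVPA per day", as support for going on to the full trial. It continues: "For this we will use a partially clustered mixed effects model with 6-month minutes of MVPA as the outcome". Baseline MVPA is a fixed effect, together with "site and randomised group as fixed effects and SPACES intervention groups as random effects". It adds: "The ICC from this model will be reported and will inform the ICC estimate for the main trial".

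The section *Methods in analysis to handle protocol non-adherence and any statistical methods to handle missing data* returns to the same endpoint. "The planned primary outcome measure for the future trial, minutes of MVPA at 6 months", it says, "will be analysed at in a multiple linear regression model to compare the intervention versus usual care". It lists no covariates and no random effect, and does not refer to the model given earlier.

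*Intervention description* explains why clustering arises: "The intervention group will include between 6–12 participants and be supported by two PACs". Usual care has no such groups. *Sample size* counts the ICC among the uncertain parameters that the study should estimate.

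**The concern.** Outcome, time point and comparison are the same in both sections, but the models differ in whether they allow for people treated in the same group being alike. A multiple linear regression, as normally understood, takes all participants as independent. If outcomes within a SPACES group are positively correlated, its confidence interval is too narrow.

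The interval for this effect is one of the inputs to the decision on a full trial. With two models and no statement of which is the main one, two intervals could be produced and the choice made after both are seen. This is not a detail left to a separate analysis plan: both models are stated in this article, which describes itself as the full protocol.

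**Working it through.** **The two statements side by side**

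- Mixed model: 6-month MVPA; fixed effects for baseline MVPA, site and arm; random effect for SPACES group; explicitly used for the 6-minute check and as the source of the ICC.
- Regression: 6-month MVPA, intervention versus usual care; no clustering term; no stated link to the 6-minute check or the ICC; not labelled main or sensitivity.

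**Inputs**

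- Sites J: 4 to 7 planned (*Sample size*); six trusts remained (*Recruitment of NHS sites*).
- Group size m: 6 to 12 (*Intervention description*).
- Allocation: 1:1 within site (*Sequence generation*).
- One intervention group per site: inferred, not stated outright.
- ICC: none given. Assumed 0, 0.01, 0.05 and 0.10.

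**The plan's own figures.** 12 participants per site over 6 months is 12/6 = 2 per site per month; 4 sites × 6 months = 24 site-months; 24 × 2 = 48, the stated lower end of the sample range. This reproduces. With 1:1 allocation, 12 per site gives 6 per intervention group. The stated upper end, 140 over 7 sites, is 20 per site and so 10 per group. Both are before attrition and invalid accelerometer wear.

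**Step 1, simple approximation.** With clustering in one of two equal arms, the true SE exceeds the regression SE by √{[2 + (m − 1)ICC]/2}.

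- ICC 0.05: m = 6, √1.125 = 1.061; m = 12, √1.275 = 1.129.
- ICC 0.10: m = 6, √1.25 = 1.118; m = 12, √1.55 = 1.245.

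Coverage as 2Φ(1.96/ratio) − 1 is then 93.5% to 91.7% at ICC 0.05 and 92.0% to 88.5% at ICC 0.10.

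**Step 2, with site as a fixed effect.** Site adjustment does not remove the problem: the group effect exists only in the intervention arm, so it enters the within-site treatment contrast. Put the group variance at ICC and the residual variance at 1 − ICC.

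- True variance = [ICC + 2(1 − ICC)/m]/J.
- Expected regression variance = 2·MS/(J·m), where MS = {2J(m − 1)(1 − ICC) + (J − 1)[(1 − ICC) + m·ICC/2]}/(2Jm − J − 1).

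For J = 6, m = 6, ICC 0.05:

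- True variance = (0.05 + 0.3167)/6 = 0.0611.
- MS = (57 + 5.5)/65 = 0.9615, so the regression variance is 2 × 0.9615/36 = 0.0534.
- SE ratio = √(0.0611/0.0534) = 1.07.

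The ratios with six sites, for m = 6 and m = 12, are:

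- ICC 0.01: 1.01 and 1.03
- ICC 0.05: 1.07 and 1.14
- ICC 0.10: 1.14 and 1.28

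**Step 3, simulation.** Coverage (%) of the nominal 95% regression interval with site fixed effects, 20,000 simulated trials per setting, baseline covariate omitted:

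| Sites, group size | ICC 0 | ICC 0.01 | ICC 0.05 | ICC 0.10 |
|---|---|---|---|---|
| 4, 6 | 95.0 | 94.9 | 93.2 | 91.3 |
| 6, 6 | 95.1 | 94.7 | 93.2 | 91.5 |
| 6, 12 | 95.1 | 94.4 | 91.3 | 87.6 |
| 7, 10 | 94.8 | 94.3 | 92.2 | 89.0 |

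At ICC 0 nothing is lost. With six sites, a true difference of exactly 6 minutes would be missed by the regression interval in 6.8% (m = 6, ICC 0.05) to 12.4% (m = 12, ICC 0.10) of trials, against the nominal 5%.

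**The case against.** The best defence is that the first section already settles which model serves the decision. It ties both the 6-minute check and the ICC to the mixed model by its own wording, while the later sentence mentions neither. That sentence is also garbled, lists no covariates and may be loose shorthand for the adjusted model described earlier. The trial is a feasibility study with a mainly descriptive analysis, its traffic-light criterion is recruitment, and the MVPA interval is one of several inputs to progression.

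Much of this stands, and it rules out three stronger readings that a reader might infer.

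- *That no ICC will be estimated.* The mixed model is still planned and its ICC is to be reported; it would be lost only if the regression replaced that model, which nothing says.
- *That the narrow interval would wave the trial through.* The check asks whether the interval includes 6 minutes. For a given estimate a narrower interval is less likely to do so, which makes the check harder to pass.
- *That coverage near 88% is to be expected.* That needs groups of 12 and an ICC of 0.10 together. The recruitment target implies groups of about 6, and at ICC 0.01 the loss is negligible.

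What the defence does not remove is the contradiction. The later sentence says the outcome will be analysed by regression, and a reader cannot tell whether that is shorthand, a second analysis or the main one.

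**Conclusion.** The point holds as an inconsistency of moderate severity. Two different models are stated for one comparison without ranking, and the one in the non-adherence and missing-data section would give too narrow an interval if the group ICC is positive. For groups of 6 to 12, coverage is about 94.5% at ICC 0.01, 91-93% at 0.05 and 88-92% at 0.10. At the group size of about 6 implied by the recruitment target, it is about 93% at ICC 0.05 and 91-92% at 0.10.

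These figures rest on assumed ICCs, one intervention group per site, equal group sizes, and a calculation without the baseline covariate. The contradiction itself rests on none of them. The text does not show that clustering is ignored by design, nor that the 6-minute check will be run on the regression.

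**What to change.** In the non-adherence and missing-data section, replace the regression sentence with a reference to the partially clustered mixed model in *Statistical methods for primary and secondary outcomes*, named as the single analysis of 6-month MVPA. Alternatively, keep the regression but label it a sensitivity analysis that plays no part in the 6-minute check. *Trial status* reports that follow-up has closed, so the record should also state when this was settled relative to the analysis.

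The edit is one sentence. The price is a wider interval than the regression would give. How to set degrees of freedom with so few groups is a separate choice that an analysis plan may already cover, and its effect need not be small: if they were near the number of groups minus one (3 to 6 for 4 to 7 groups), the t multiplier would be about 3.18 to 2.45 instead of 1.96.
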